### Step 3: choice task construction

In each DCE choice task, respondents are presented with two hypothetical treatment profiles and asked to select their preferred alternative. During the attribute development phase (see Section 2.2), a total of 14 patient-relevant attributes were identified. Considering that health-related DCE studies typically employ 4–6 attributes, we opted for a partial profile DCE design to reduce the complexity of the choice tasks (35). In this design, each choice task encompasses 4 of the 14 attributes, with each attribute having 2 to 5 varying levels. Furthermore, to minimize the difficulty of the survey and to ensure a manageable task for participants, we included a maximum of two unlabelled treatment alternatives displayed as “Treatment A” and “Treatment B.” No opt-out option was included to preserve preference information in each DCE choice task and to prevent loss of information when participants opt-out.

The combination of attribute levels and treatment options presented in each DCE choice question were generated by Sawtooth Software's randomized balanced overlap design. This random design includes some degree of attribute level overlap, which has shown to reduce dropout rates, to increase the level of choice consistency, and to avoid learning effects (36). Further, the use of attribute level overlap is a recommendable strategy to reduce attribute non-attendance e.g., ignoring one or more of the included attributes, resulting in deeper preference information than minimal overlap (37, 38). Dominant alternatives where the attribute levels of one alternative are clearly better than the attribute levels of the other alternative were manually excluded from the balanced overlap design. In the final survey, each respondent received a set of one of the 295 combinations of choice tasks.

### Step 4: sample size estimation

A priori sample size calculations for DCE experiments remain a significant challenge (35). Typically, DCE questionnaires necessitate larger sample sizes compared to other preference elicitation methods, often exceeding 250 participants (20). The minimal required sample size is contingent upon various factors such as the complexity of the choice tasks, the number of DCE questions, preferred precision of the results, the need for subgroup analysis, and the desirability to measure interactions. Recognizing this, we explored the capabilities of Sawtooth's test design option, which provides sample size calculations including estimated precision of the results based on choice task complexity and the number of DCE questions, revealing an inverse relationship between the latter and the anticipated sample size. This led to a trade-off discussion with our advisory board, weighing the number of expected respondents with the amount of DCE choice questions that we could include while keeping the survey as short and cognitively manageable as possible. Ultimately, the advisory board anticipated to be able to recruit minimally 700 patients globally. This estimation was made based on previous experience with quantitative research in the targeted patient population and the global disease burden of IBD, which is estimated to be between 2.5 and 3 million people in Europe alone (3). Consequently, each participant in our survey will need to complete 15 choice questions, aligning with ISPOR guidelines for conjoint analysis applications in health (27). This strategy was implemented to secure statistically significant responses and to achieve our study objectives.

### Step 5: survey implementation

The overall survey was implemented in Lighthouse studio with Sawtooth software (39). The survey consisted out of 10 parts: (1) language selection, (2) introduction to the survey, (3) screening questions, (4) information sheet and informed consent form, (5) explanation of the attributes and levels included in the survey, (6) DCE questions (see Section 2.3), (7) feedback on the DCE questions, (8) validation question, (9) questions on patients socio-demographic characteristics, clinical characteristics, and contextual factors, and (10) survey evaluation questions.

Questions on patients' socio-demographic characteristics (e.g., age, age of diagnosis, sex, and work status), clinical characteristics (e.g., disease status, current treatment, previous treatment, and surgical history), and contextual factors (e.g., distance to from location were followed for treatment, involvement in treatment decision-making, knowledge about disease) will be asked as such that preference heterogeneity can be explained. Further Chews' set of brief screening questions were included to determine the health literacy of participants and to identify patients who may face challenges in comprehending medical information (40). All questions were formulated in collaboration with the advisory board, providing valuable input to improve patient relevance and optimize wordings, ultimately reducing cognitive burden while ensuring clinical relevance. The advisory board also reviewed the information sheet and informed consent form. The validation question and time to complete the survey were built into the survey as validity checks.

### Step 6: piloting

The programmed survey was piloted with four native speaking English patients. Online pilot interviews were organized using the think-aloud method that evaluated (1) patients' comprehensibility of the general survey questions, (2) patients' understanding of the choice questions (including the attributes and their descriptions) and the explanation preceding the choice questions, (3) patients' choice behavior, and (4) the length of the survey. After each interview, feedback was discussed with the advisory board until consensus was reached and the survey was iteratively adapted before the next pilot. After the fourth pilot, no further changes were deemed necessary, and the piloting stopped.

Overall, participants thought that the survey was easy to read, had a good flow, and was user-friendly with graphics supporting the content. Utilizing the suggestions and opinions shared by participants, the first information page was made more concise and emphasize was placed on the option to receive background information by clicking on specific words. Moreover, some repetitions were highlighted, and the questions were adapted accordingly. Lastly, the validation question was adjusted from “Which 3 characteristics are most important to you” to “In the previous questions we asked you to choose between two treatments that differed according to the characteristics that are listed below. Which 3 characteristics do you think are most important and did you consider the most when answering the previous questions?”. Besides textual errors in the demographic questions, which were rectified promptly, participants did not report any other concerns regarding the general questions.

Participants found the DCE questions to be “Very easy” or “Easy” to understand. However, some participants indicated that it was “Difficult” to answer the choice questions, explaining that this was due to the nature of the questions and the complex trade-offs they had to make. Based on the feedback during the pilots, the explanation proceeding the choice questions was adapted to provide more clarification. In addition, the attribute “achievement of long-term endoscopic remission” was renamed to “presence of visual signs of inflammation in the bowel” as the original attribute was deemed not clear. Further, an explanation for the word “striae” in the explanation of the attribute “duration of severe skin problems” was added and some revisions in the wording of the levels and explanations were carried out. Participants found the survey length “manageable” or “too long,” with two participants needing more than 30 min to complete the survey. These participants may have required more time due to the additional task of evaluating the survey.

During the pilots, special attention was given to the choice behavior of participants to detect the possible occurrence of simplifying heuristics e.g., choice processes that do not adhere to the normative rationality assumptions implied by RUT as participants apply simplifying decision rules. During the pilot interviews, participants did not show simplifying heuristics that are common in (health-related) DCEs such as attribute non-attendance (respondents completely ignore certain attributes), choice set formation (elimination of choice alternatives based on certain threshold levels for particular attributes), and lexicographic preferences (selecting alternatives entirely based on their superiority on one most important attribute) (24).

### Step 7: translation

The final English survey was translated by a native speaking researcher of this study or national patient organization member into Arabic, Croatian, Danish, Dutch, Finnish, French, German, Greek, Hungarian, Italian, Polish, Portuguese, Romanian, and Spanish (total languages = 15). A mix between North, East, South, and West European languages was chosen to increase heterogeneity and inclusiveness of participants in terms of different European regions, ensuring representativeness of the patient sample. Furthermore, the survey was translated to Arabic, English, French, Portuguese, and Spanish as such that also patients outside of Europe were able to complete the survey.

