### Recruitment

The survey will be widely disseminated across the world to reach a large and heterogenous sample of IBD patients. Patients will be recruited via the IBD umbrella patient organization EFCCA, national patient organizations, and local clinicians. These recruiting parties will disseminate the survey link via mail, newsletters, social media, and face-to-face hospital visits.

The survey includes initial questions to assess the eligibility of the participants using the following criteria:

Patients diagnosed with Crohn's disease, ulcerative colitis, or inflammatory bowel disease type unclassified;Adult patients (≥18 years old);Able to understand the language used in the survey; andApproval of the informed consent.

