### Data analysis plan

The main goal of the patient preference survey is: (1) to determine the relative preference weights for IBD treatment and disease related attributes, and (2) to explain preference heterogeneity by investigating how preferences may be influenced by socio-demographic characteristics, clinical characteristics, and contextual factors.

To determine the preferences of IBD patients, attribute (level) estimates, and the relative importance of each attribute, a logit-based analysis strategy will be applied and conditional logit (CL), latent class (LC), and mixed logit (ML) models will be fitted. The final decision on modeling will be made once data collection is finished. This decision will be made based on the model's conformity to the data and its clinical interpretation. It is possible that different models will be used to address the various research questions. Preference heterogeneity and the impact of socio-demographic characteristics, clinical characteristics, and conceptual factors will be explained by applying LC analysis and/or subgroup analysis. All results above will be compared between countries, gender, and IBD subtype.

Descriptive analysis using mean and standard deviations will be used to summarize the responses on the closed survey questions. Responses to the open questions will be analyzed qualitatively using the thematic analysis (41).

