### Ethical considerations

Prior to the focus group discussions, all participants provided their informed consent. To protect participants' privacy, all participants were identified by a number and not by their name. After transcription, all audio recordings were destroyed. Survey participants will be informed that their participation in the patient preference survey is pseudonymous (no names or IP addresses will be asked, however, responses in the open text fields may enable the researchers to recognize participants) and have the possibility to read the information sheet outlining detailed information about the study. They will then be asked to provide electronic informed consent before they can answer any further questions in the survey. It is possible that participants may become distressed thinking about IBD and the associated impact that the disease or its treatment may have or has had on their lives. Therefore, we will provide participants sources for further information and contact details for support.

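### Offering the survey in many European languages widens access but cannot make a self-selected link sample representative, so the claim and the conclusions built on it should be narrowed.

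*Protocol article*

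**What the plan says.** Under Step 7: translation, the article explains that languages from North, East, South and West Europe were chosen "to increase heterogeneity and inclusiveness of participants in terms of different European regions, ensuring representativeness of the patient sample". Five of the 15 languages are also said to open the survey to patients outside Europe.

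The Recruitment section sets a more modest aim: "The survey will be widely disseminated across the world to reach a large and heterogenous sample of IBD patients". On entry to the sample it says: "Patients will be recruited via the IBD umbrella patient organization EFCCA, national patient organizations, and local clinicians". On distribution: "These recruiting parties will disseminate the survey link via mail, newsletters, social media, and face-to-face hospital visits". On eligibility: "The survey includes initial questions to assess the eligibility of the participants using the following criteria".

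The Data analysis plan proposes conditional logit, latent class and mixed logit models to determine the preferences of IBD patients, and then states: "All results above will be compared between countries, gender, and IBD subtype". The Abstract, Introduction and Discussion describe a global study whose results should serve drug development, regulatory approval and reimbursement.

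**The concern.** Representativeness concerns who enters a sample and in what proportions. The set of languages bears only on who is able to answer. Within each language the respondents are those whom a recruiting party reaches and who choose to take part. Members of patient organisations and people active online may differ from other patients in disease severity, treatment history or health literacy, and the study itself expects such characteristics to influence preferences.

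Step 7 thus asserts a property that the recruitment described in the same article cannot deliver. At stake is what may be concluded. A regulator or HTA body that takes the statement at face value would read an overall set of weights as those of IBD patients in general, when they are the weights of the patients who responded. A larger sample narrows the interval but leaves this gap in place.

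**Working it through.** **1. The statements side by side**

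| Section | What it supports |
|---|---|
| Step 7: translation | Representativeness, attributed to the choice of languages |
| Recruitment, aim | A large and varied sample |
| Recruitment, route | Volunteers reached by a link passed on by organisations and clinicians |
| Recruitment, eligibility | Screening questions inside the survey |
| Data analysis plan | Comparison by country, gender and subtype |

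A varied sample can still have the wrong proportions. None of the last four rows fixes the proportions, so none supports the first. Reading Step 7 as limited to European regions does not change this: a Polish or a Danish version does not set the share of Polish or Danish respondents, or decide which patients in those countries answer.

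**2. How the mix enters a pooled estimate**

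The article gives no figure to reproduce here; 700 is the number the advisory board expected to recruit. Let one group have share s among respondents and share p in the target population, and let its coefficient differ from that of the rest by d logits. Treating the unweighted pooled coefficient as approximately a share-weighted average,

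shift ≈ d × (s − p).

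The values of s, p and d below are assumptions; none is in the article.

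| s | p | d = 0.25 | d = 0.5 | d = 1.0 |
|---|---|---|---|---|
| 0.20 | 0.20 | 0 | 0 | 0 |
| 0.20 | 0.10 | 0.025 | 0.05 | 0.10 |
| 0.40 | 0.20 | 0.05 | 0.10 | 0.20 |
| 0.40 | 0.10 | 0.075 | 0.15 | 0.30 |
| 0.60 | 0.20 | 0.10 | 0.20 | 0.40 |
| 0.60 | 0.10 | 0.125 | 0.25 | 0.50 |

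**3. Scale against sampling error**

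Inputs from the article: 700 respondents, 15 choice questions each, 4 of 14 attributes per question. An attribute is shown in 700 × 15 × 4/14 = 3,000 tasks. Assume that in 30–50% of these both alternatives carry the same level, leaving 2,100 to 1,500 informative tasks. With choices near 50:50, each contributes about 0.25 units of information on a two-level attribute, so

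SE ≈ 1/√(0.25 × 2,100) = 0.044 to 1/√(0.25 × 1,500) = 0.052,

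and the 95% half-width is 1.96 × SE ≈ 0.09 to 0.10. This ignores clustering within respondents and choices far from 50:50, so it is a rough guide. Several of the assumed shifts above equal or exceed it; others fall well below.

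**4. What the planned comparisons can do**

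They can show that preferences differ between countries or subtypes. They do not reweight an overall estimate, and they do not address selection within a country. They will also be less precise. Spread evenly over 15 languages, 700 respondents is about 47 per language, and the half-widths above grow by √15 ≈ 3.87, to about 0.33–0.39. The number of countries is not stated, so languages serve only as a rough stand-in.

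**The case against.** The strongest reply is that this is one clause in a sentence about European regions, that the Recruitment section claims no more than a varied sample, and that heterogeneity by country, gender and subtype is already in the analysis plan. Most of this is fair. The choice design is untouched, and the comparisons go some way towards showing whether the mix matters. But the clause is stated without qualification, and the comparisons describe differences without correcting an overall figure.

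A second reply is that the article never promises a single global weight. That is correct, so the point is confined to any overall estimate that is reported. The Data analysis plan speaks first of the preferences of IBD patients and then of comparing those results, which makes an overall estimate likely but not certain.

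A reader might go further and infer that repeat or non-patient entries could never be detected, because "no names or IP addresses will be asked". The document does not support that. Not asking for IP addresses does not exclude other controls. The article is a condensed account whose survey supplement and data management plan are not shown, so its silence on link tagging or repeat-entry control is no finding. It also says: "The validation question and time to complete the survey were built into the survey as validity checks". Nor does it follow that invalid entries would pull every coefficient towards zero. That applies to random clicking, not to a patient who answers twice, and a uniform shrinkage largely cancels in relative weights, which are what the study seeks.

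**Conclusion.** The point holds in limited form. The article attributes representativeness to its choice of languages while describing a self-selected convenience sample, and the first cannot follow from the second. Any overall estimate carries the mix of those who respond.

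The size of the consequence cannot be established from the document. It is nil if shares match or preferences are alike. The illustrative shifts rest wholly on assumed shares and differences, and show only that the effect could be as large as sampling error or larger. It would be wrong to read them as a predicted bias, or to treat the 15 languages as 15 countries of equal weight; no population shares are given. The matter is worth correcting because the intended readers make regulatory and reimbursement decisions and the correction is cheap. It does not call the choice experiment into question.

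**What to change.** - In Step 7, replace the representativeness clause with a statement that the languages broaden reach across European regions and beyond.
- In Recruitment, describe the sample as a convenience sample of volunteers, and limit conclusions about IBD patients globally accordingly.
- Report any pooled estimate beside the planned country and subtype results.
- Add one sensitivity version standardised to a region and Crohn's disease/ulcerative colitis mix fixed before the data are seen, with the source of the mix and the handling of unclassified disease stated. This adjusts only for region and subtype; selection within those groups remains, so the convenience-sample description must stay.

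The cost is a weaker claim, one additional analysis and somewhat wider intervals for the standardised version. As an illustration with the assumed shares above, moving a group from 40% to 20% gives weights 0.20/0.40 = 0.5 and 0.80/0.60 = 1.33. The variance factor is 0.4 × 0.5² + 0.6 × 1.33² ≈ 1.17, so intervals widen by √1.17, about 8%. Moving it from 40% to 10% gives weights 0.25 and 1.5, a factor of 0.4 × 0.25² + 0.6 × 1.5² = 1.375, and intervals about 17% wider. Neither the survey nor the choice tasks need to change.

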### Step 8: pre-testing

After programming the survey into the 15 different languages in Sawtooth, the advisory board and native speaking patients (representatives) that helped with the translations cross-checked the programmed survey during the pre-testing phase to final test the functionality of the survey program and identify textual errors. No significant issues were identified, and only minor textual revisions were implemented. The final survey can be found in Supplementary material 4.

### Recruitment

The survey will be widely disseminated across the world to reach a large and heterogenous sample of IBD patients. Patients will be recruited via the IBD umbrella patient organization EFCCA, national patient organizations, and local clinicians. These recruiting parties will disseminate the survey link via mail, newsletters, social media, and face-to-face hospital visits.

The survey includes initial questions to assess the eligibility of the participants using the following criteria:

Patients diagnosed with Crohn's disease, ulcerative colitis, or inflammatory bowel disease type unclassified;Adult patients (≥18 years old);Able to understand the language used in the survey; andApproval of the informed consent.

### Data analysis plan

The main goal of the patient preference survey is: (1) to determine the relative preference weights for IBD treatment and disease related attributes, and (2) to explain preference heterogeneity by investigating how preferences may be influenced by socio-demographic characteristics, clinical characteristics, and contextual factors.

To determine the preferences of IBD patients, attribute (level) estimates, and the relative importance of each attribute, a logit-based analysis strategy will be applied and conditional logit (CL), latent class (LC), and mixed logit (ML) models will be fitted. The final decision on modeling will be made once data collection is finished. This decision will be made based on the model's conformity to the data and its clinical interpretation. It is possible that different models will be used to address the various research questions. Preference heterogeneity and the impact of socio-demographic characteristics, clinical characteristics, and conceptual factors will be explained by applying LC analysis and/or subgroup analysis. All results above will be compared between countries, gender, and IBD subtype.

Descriptive analysis using mean and standard deviations will be used to summarize the responses on the closed survey questions. Responses to the open questions will be analyzed qualitatively using the thematic analysis (41).

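### Comparing logit level estimates between countries, genders and IBD subtypes can mistake differences in response noise for differences in preference

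*Protocol article*

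**What the plan says.** The Data analysis plan defines its outputs in one sentence: "To determine the preferences of IBD patients, attribute (level) estimates, and the relative importance of each attribute, a logit-based analysis strategy will be applied". The models are listed next: "conditional logit (CL), latent class (LC), and mixed logit (ML) models will be fitted". The choice among them is left open: "The final decision on modeling will be made once data collection is finished", on the basis of fit to the data and clinical interpretation.

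For the second aim, preference heterogeneity "will be explained by applying LC analysis and/or subgroup analysis". The paragraph then closes with the sentence at issue: "All results above will be compared between countries, gender, and IBD subtype". Level estimates are among the results listed before that sentence, so they are among the quantities to be compared between groups.

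The article does not mention scale or error variance. It does not limit the comparison to quantities that are free of scale.

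**The concern.** In a random-utility logit model the error variance is not identified separately from the coefficients. What is estimated in group g is λ_g × β, where β is preference and λ_g is the scale, which falls as the error variance rises. Two groups with the same β and different λ give different level estimates on every attribute that matters to them. The group that answers more noisily seems to care less about everything.

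Unequal noise is plausible here. The survey runs in 15 languages. The pilot that examined comprehension and choice behaviour covered English only: "The programmed survey was piloted with four native speaking English patients". Under Step 8, the programmed language versions were cross-checked for functionality and textual errors by the advisory board and by the native speakers who had helped translate. That is useful, but it does not test how patients make the choices. Recruitment ranges from social media to hospital visits. Health literacy is measured but is not tied to the group comparisons.

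At stake is part of the second aim: a country or subgroup could be described as placing less weight on, say, surgery risk or fatigue when its answers are only less consistent.

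**Working it through.** **Inputs from the protocol article**

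- Sample (Step 4): "the advisory board anticipated to be able to recruit minimally 700 patients globally".
- Tasks (Step 4): "each participant in our survey will need to complete 15 choice questions". That gives 700 × 15 = 10,500 choices.
- Tasks show two alternatives and 4 of 14 attributes (Step 3), so each attribute is seen 15 × 4 / 14 = 4.3 times per respondent.
- Table 3 has nine attributes with 2 levels, four with 3 and one with 5. Levels: 18 + 12 + 5 = 35. Coefficients: 35 − 14 = 21.

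The plan gives no scale ratio, alpha or effect size for these comparisons, so it has no figure of its own to reproduce.

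**Algebra**

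- Level estimate in group g: λ_g β. It depends on λ_g.
- Relative importance of attribute a: λ_g range_a / Σ(λ_g range) = range_a / Σ range. Scale cancels.
- Trade-off ratio: λ_g β_a / (λ_g β_b) = β_a / β_b. Scale cancels.

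Example: a level effect of 0.8 logit is estimated around 0.8 × 0.8 = 0.64 in a group with scale ratio 0.8, and around 0.7 × 0.8 = 0.56 at ratio 0.7, with no change in preference.

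**Simulation of the stated design**

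Two groups of 350 have identical preferences and differ only in scale. A conditional logit is fitted to each. Each of the 21 coefficients is tested at 5%, then all jointly by likelihood ratio. The joint test is repeated with one free relative-scale parameter (Swait-Louviere type). That test has 42 − 22 = 20 degrees of freedom: two sets of 21 coefficients against one set plus a scale.

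Assumptions not in the documents: the 350/350 split, attribute utility ranges of 0.3 to 1.5 logit, random level assignment without removal of dominant pairs, no within-person correlation, and the scale ratios. There are 60 replicates per row.

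| Scale ratio | Coefficients falsely differing (of 21) | Joint test rejects | Joint test rejects, scale freed | Estimated ratio |
|---|---|---|---|---|
| 1.0 | 1.2 | 7% | 5% | 1.00 |
| 0.9 | 2.1 | 22% | 5% | 0.90 |
| 0.8 | 5.0 | 85% | 2% | 0.80 |
| 0.7 | 8.6 | 100% | 3% | 0.70 |
| 0.5 | 12.9 | 100% | 3% | 0.50 |

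Chance alone gives 21 × 0.05 = 1.05 in the second column. The Monte Carlo standard error of a 5% rate is √(0.05 × 0.95 / 60) = 2.8 points, so the scale-freed column is consistent with 5%.

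Further runs with 350 per group, including some with every attribute effect at 0.8 logit, gave 3.8 to 5.4 coefficients and 58% to 70% joint rejection at ratio 0.8. At ratio 0.7 they gave 8.0 to 9.3 coefficients and 97% to 100%. The joint rate varies between runs, but in all of them it is far above 5%.

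The mean absolute gap in estimated relative importance was 0.80 points at ratio 1.0, 0.95 at 0.7 and 1.18 at 0.5. The true gap is zero throughout, so the increase is mostly sampling noise.

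**Smaller groups**

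The number of countries is not stated. Purely for illustration, 700 / 15 ≈ 47 per group:

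- 47 v 47, equal scale: 1.1 of 21.
- 47 v 47, ratio 0.8: 1.4 to 1.5 of 21; joint test rejects 9% to 13%.
- 47 v 47, ratio 0.7: 2.0 of 21; joint 19%.
- 47 v 653, ratio 0.8: 1.8 of 21; joint 23%.

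The shrinkage of the level estimates is the same as in large groups. Only the chance of its reaching significance falls.

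**The case against.** The strongest reply is that this is a condensed article with no SAP shown. It says only that results will be compared, names no test, and leaves the model open. A scale test is a detail an SAP could well hold. That stands as far as it goes: the article's silence does not prove that the analysts will ignore scale. It does not dispose of the point, because the sentence itself puts level estimates among the quantities to be compared. Nor does the deferred model choice settle it: fit and clinical interpretation do not address scale, and ordinary latent class or mixed logit models do not separate it between predefined groups.

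Several stronger readings are tempting, and the documents do not support them:

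- A reader might infer that noise *will* be reported as preference. That requires the groups to differ in scale, and the documents give no figure for this.
- A reader might infer that every between-group result is compromised. Relative importance is one of the two named outputs and is unaffected.
- A reader might infer that the whole second aim rests on these comparisons. It also rests on latent class and/or subgroup analysis over a wider set of characteristics.
- A reader might apply the 350 v 350 figures to every country. The reasons for unequal noise are strongest between language versions, where groups may be small and false significance is much less frequent. For gender and subtype, where groups may be large, the documents give no specific reason for scale to differ.
- A reader might count false positives over all coefficients and countries. The number of countries is not given, and the plan states no coefficient-by-coefficient testing at 5%.

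**Conclusion.** The point holds for raw level estimates only. As written, the plan compares between groups a quantity that mixes preference with response noise, so a difference in noise can appear as a difference in preference.

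Under assumed scale ratios, identical preferences and two groups of 350, about 4 to 5 of 21 coefficients falsely differ at ratio 0.8 and about 8 to 9 at 0.7, against about 1 by chance. With about 50 per group the count is close to chance at 0.8 and about 2 at 0.7. Whether any of this occurs depends on the actual scale differences, which are unknown. This is a worthwhile correction to one sentence. It does not undermine the survey or the estimation of overall preference weights.

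**What to change.** Amend the closing sentence of that paragraph in the Data analysis plan, before any group results are seen, along these lines:

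> *Comparisons between countries, genders and IBD subtypes will use relative importances or within-group trade-off ratios with confidence intervals, or a pooled model with group-by-attribute interactions and a group-specific scale parameter (Swait-Louviere test or heteroscedastic logit). Raw level estimates will not be compared across groups unless equal scale is supported.*

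One technical note: if every coefficient is interacted with group, a group scale cannot be identified as well. The Swait-Louviere route avoids this by testing separate fits against common preferences with a free scale. Otherwise, at least one coefficient must be held common across groups.

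The cost is a change of wording, slightly more modelling and fewer nominally significant differences. The survey, choice design and sample size are unchanged.
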